### CHSGS + paroxetine group

Patients will be provided three-daily treatment with 5 g CHSGS added to the 5 red capsules and one-daily treatment with 30 mg paroxetine added to the yellow capsule each time until 4 weeks.

### Placebo group

Patients will be provided three-daily treatment with 5 g mixed starch powder added to the 5 red capsules and one-daily treatment with 5 g mixed starch powder added to the yellow capsule each time until 4 weeks.

It is well - recognized that placebos serve as the optimal comparator in clinical controlled trials. Consequently, we incorporated this placebo and standardized its characteristics. The placebo components were obtained from the Chongqing Traditional Chinese Medicine Hospital. The materials of placebo are starch and place the mixed starch powder into a container, add honey and stir well to make it into capsule. The above materials made shared the same character with the CHSGS capsule and paroxetine in terms of appearance, weight and taste.

### MRI scan

A GE3.0T magnetic resonance scanner (General Electric Company, America) at the Chongqing Traditional Chinese Medicine Hospital and a head orthogonal coil were used for 2 scans before and after treatment. A single excitation gradient echo planar imaging sequence was used for acquisition. The parameters were: TR/TE: 2000 m/30 m, FOV: 240 mm, matrix size: 64 × 64, flip angle: 90°, in-plane resolution: 3.75 mm × 3.75 mm, slice thickness: 5 mm thick with no gaps, and 32 sagittal slices.

### Outcome assessment

Independent assessors, who received standardized training prior to study involvement and remained blinded to group allocations throughout the trial, will evaluate all clinical outcomes. Comprehensive participant data - including both completers and those who discontinued intervention - will be systematically documented in electronic case report forms (CRF), ensuring complete tracking of all enrolled subjects.

### Primary outcome

Drawing on a range of clinical studies, the assessment will be carried out on all patients. Specifically, for patients with APE (Premature Ejaculation), the mean changes from the baseline (the day when the patient commences the protocol) to the end of the observation period (the day when the protocol concludes) will be evaluated in two aspects: the brain MRI and the intravaginal ejaculatory latency time (IELT) measured using a stopwatch, which has been extensively applied and is recommended as a primary outcome measure in clinical trials for APE.

### Secondary outcome

In terms of the assessment of symptom severity of APE for all the participants in this study, the secondary outcome will be based on the premature ejaculation profile (PEP) and Chinese Index of Premature Ejaculation (CIPE). In order to assess the patients’ TCM evidence and the degree of improvement, this trial also introduced the TCM syndrome score as a secondary outcome.

### Adverse events

During the trial, observers will properly estimate and record adverse events (AEs) associated with paroxetine treatment, including but not limited to vertigo, headache, and blurred vision. A specialized practitioner, who is not involved in clinical data analysis, will manage these AEs within 24 h. In the event that severe AEs occur, the principal researcher will make the final decision on whether to terminate the trial.

All data related to the participants during the study, as well as details of related and unexpected AEs (such as the time of occurrence, AE severity, and suspected causes), will be collected and documented in the Case Report Form (CRF). Depending on the severity of the AEs, the measures can range from providing symptomatic treatment to submitting the case to the Research Ethics Committee within 48 h.

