Selective serotonin reuptake inhibitors, such as dapoxetine and paroxetine, have been shown to delay ejaculation. Paroxetine, as a selective 5-hydroxytryptamine (5-HT) reuptake inhibitor, can regulate central nervous activity by elevating the level of 5-HT in the synaptic gap, inhibit the ejaculatory reflex from the spinal cord level, improve the control of ejaculation, and prolong the ejaculatory latency period (Raveendran and Agarwal, 2021). Emerging research indicates that paroxetine administration could modulate neurofunctional dynamics in major depressive disorder, particularly influencing amygdala reactivity and functional connectivity patterns within associated neural networks (Tassone et al., 2024). However, these medications carry the risk of side effects and can be expensive. As a result, many patients have poor compliance, which makes it much more difficult to treat the disease (Niu et al., 2024).

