#### Dropout criteria

1. The occurrence of serious adverse events, complications and special physiological changes, it is not suitable to continue to receive the trial2. The trial process of self-withdrawal3. Due to a variety of reasons caused by the end of the course of treatment, namely, withdrawal from the trial, lost to visit the case4. Incomplete information, affecting the effectiveness and safety of the judgment.The reason for removal should be recorded in all cases of exclusion or detachment. Any adverse reactions during treatment are included in the adverse reaction statistics.

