### Randomized

Eligible participants will be randomly allocated to one of four groups in a 1:1:1:1 ratio: the paroxetine group, CHSGS group, CHSGS + paroxetine group, or placebo group. Randomization will be performed using SAS V.9.3 software, with sequences generated by an independent third party not involved in participant management, outcome assessment, or data analysis. Group assignments (denoted as A, B, C, or D) will be sealed in sequentially numbered, opaque envelopes prepared by a researcher unaffiliated with the trial. These envelopes will remain securely stored in numerical order until the study concludes to ensure allocation concealment. Access to the randomization codes will be restricted until final data analysis to maintain blinding integrity.

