### Blinding

To ensure blinding in this study protocol, double - blind tests will be employed. Specifically, sham paroxetine and sham CHSGS capsules will be prepared. The Pharmacy Department of the Hospital of Chongqing Traditional Medicine Hospital will handle and label the medications in a special way. This is to guarantee that both the patients and the practitioners involved in the study remain completely unaware of the identity of the treatment being administered. Moreover, all practitioners are prohibited from communicating with the participants about the information related to this trial.

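### The adverse-event section limits recording to paroxetine-associated events, omits the test product CHSGS, and conflicts with the protocol's other safety wording

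*Protocol article*

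**What the plan says.** Four places in the protocol article bear on which adverse events are captured.

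- **Adverse events, first paragraph:** "observers will properly estimate and record adverse events (AEs) associated with paroxetine treatment". Examples of symptoms follow; their list is open, but the class they illustrate is tied to paroxetine. CHSGS is not named anywhere in the section.
- **Adverse events, second paragraph:** for the case report form, "details of related and unexpected AEs (such as the time of occurrence, AE severity, and suspected causes), will be collected and documented". No drug is named.
- **Dropout criteria, closing sentence:** "Any adverse reactions during treatment are included in the adverse reaction statistics". Again no drug is named.
- **Table 1:** one adverse-event row covers weeks 1 to 4 plus a call-back in week 5, with no split by arm.

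On the design, "Eligible participants will be randomly allocated to one of four groups in a 1:1:1:1 ratio": paroxetine, CHSGS, both, or placebo. The Blinding section requires that "both the patients and the practitioners involved in the study remain completely unaware of the identity of the treatment being administered".

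**The concern.** The first sentence is a positive instruction about what to record, so it is not a detail left to a fuller document. It describes the safety interest of the active control and leaves out the product under test.

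It also cannot be carried out as written. An observer who does not know who takes paroxetine can only ask whether a symptom looks like a known paroxetine effect. That question suits paroxetine-type symptoms in any arm. It does not suit an event peculiar to the herbal formula, or to the formula given with paroxetine, if the observer does not recognise it as a paroxetine effect.

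At stake is the completeness of the safety record for the 42 patients who receive CHSGS. The Data Monitoring Committee named under Data monitoring and management would see only what was recorded, and an event not written down at the time cannot be recovered at analysis.

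**Working it through.** The plan states no figure on this point, so there is none to reproduce. The check is mainly one of wording.

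**1. The statements side by side**

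| Place | Scope | Drug named | Attribution required |
|---|---|---|---|
| Adverse events, first paragraph | events associated with paroxetine | paroxetine | yes, to one drug |
| Adverse events, second paragraph | related and unexpected events | none | yes; unclear whether either or both conditions are needed |
| Dropout criteria | any adverse reaction during treatment | none | implied by the word reaction |
| Table 1 | timing of contacts | none | silent |

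**2. Patients concerned.** With 21 per arm and four arms, the total is 4 × 21 = 84. CHSGS is given in the CHSGS arm and the combination arm: 2 × 21 = 42. Paroxetine is also given to 42, and the combination arm belongs to both counts.

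**3. One event taken through the wording.** Suppose a blinded observer sees a symptom and suspects the herbal formula, not paroxetine.

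- First paragraph: outside the scope.
- Second paragraph: inside if related or unexpected is enough; if both are needed, inside only when the event is also unexpected.
- Dropout criteria: counted as an adverse reaction, but statistics can count only what was recorded.

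The same event is treated differently according to the sentence used. An event judged unrelated to any study product, and not unexpected, is plainly required by none of them.

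**4. Where a gap could arise.** Under blinding, paroxetine-type symptoms would be recorded in every arm, including CHSGS alone and placebo. In the combination arm they also fall squarely within the first sentence. The possible gap is confined to events not thought typical of paroxetine.

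**5. Illustration with assumed values.** The documents give no adverse-event rates. Let p be the true risk of such an event per patient in a 21-patient arm, and f the fraction of these events that is recorded. Then

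P(at least one recorded) = 1 − (1 − p·f)^21.

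For p = 10% and f = 0.5 this is 1 − 0.95^21 = 0.659, or 66%.

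| p (assumed) | f = 1 | f = 0.5 | f = 0.25 | f = 0 |
|---|---|---|---|---|
| 5% | 66% | 41% | 23% | 0% |
| 10% | 89% | 66% | 41% | 0% |
| 20% | 99% | 89% | 66% | 0% |

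If staff follow the wider sentences, f is near 1 and little or nothing is lost. If they follow the first sentence strictly, f could be low. The documents do not fix f, so the table shows how much depends on it and does not estimate the loss.

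**The case against.** The strongest defence is that the first sentence does not stand alone. It does not say that other events are to be ignored. The second paragraph of the same section asks for suspected causes without naming a drug, and its mention of unexpected events sits badly with a filter for known paroxetine effects. That sentence also sends participant data in general to the case report form. The Dropout criteria wording would cover a reaction to CHSGS. The Outcome assessment section asks for comprehensive data on completers and discontinuers, and Table 1 schedules the same contacts in every arm.

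Much of this stands. A reader might infer that events are recorded solely when tied to paroxetine; the other sentences contradict that. What they do not do is settle the matter. Two of them still depend on attribution. The general statements concern whose data are kept and when contacts occur, not which events must be written down.

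A reader might also infer that the safety comparison is biased in favour of CHSGS. The documents do not support that as a fact. The aims at the end of the Introduction concern efficacy and fMRI, safety is not among the listed outcomes, and no between-arm safety comparison is described. The Introduction says of SSRIs, "However, these medications carry the risk of side effects", but does not claim that CHSGS is safer.

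Nor can one apply a guessed event rate to the 42 CHSGS patients and call the result lost events. That would assume total non-recording, and any unrelated events included would be expected in placebo patients too.

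**Conclusion.** The point holds as an internal conflict in a rule that is badly fixed. The first sentence of the Adverse events section limits recording to paroxetine-associated events, leaves out the test product, and asks blinded observers for an attribution they cannot make from knowledge of treatment. It disagrees with the section's second paragraph and with the Dropout criteria, and no section plainly requires that every adverse event be recorded.

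The consequence is a risk: events not thought typical of paroxetine in the CHSGS and combination arms may go unrecorded. This rests on one assumption, that staff apply the first sentence literally. The size of any loss cannot be derived from the documents. It ranges from none, if the wider wording is followed, to complete for that class of event if it is not.

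**What to change.** Reconcile the three statements by rewording the Adverse events section, for example: all adverse events in all four groups, whatever the suspected cause, are recorded in the same way at the week 1 to 4 contacts and the week 5 call-back; relatedness to study treatment is judged by staff who remain blind; adverse events are counted by randomised arm. Symptoms known for paroxetine can stay as examples, provided they no longer define what is recorded. The second paragraph and the closing sentence of the Dropout criteria should then use the same scope, so that related events become a subset of all recorded events.

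No new contacts are needed, because Table 1 already has them in every arm. The cost is a short change of wording and slightly more case-report-form work. It should be in place before recording starts, since missed events cannot be restored later.

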### Quality control and data collection

Since any nonstandard or biased input of clinical data can significantly influence the bias of results, two practitioners, whose roles are to assess the treatment effect and data authenticity, will independently collect data using case report forms and original brain MRIs. The data thus gathered will be input into a dedicated computer. This entire process is designed to maximize the reliability and safety of all the data. To ensure the quality of the study, all practitioners involved must hold an official license and have at least 2 years of experience in protocol study and clinical practice.

### Data analysis

#### Clinical variables analysis

Two blinded evaluators will conduct the analysis of clinical data using SPSS 22.0 (SPSS Inc., Chicago, IL). Missing data analysis will be carried out in accordance with the intention - to - treat (ITT) principle, taking into account the baseline characteristics.

The clinical scores of the subjects will be examined through Pearson correlation analysis. All clinical data in this study will be presented in the following ways:1. Continuous measurement data will be presented as the mean ± standard deviation (SD), along with the mean, SD, median, and interquartile range.2. Categorical data will be presented as counts and percentages.

The following analysis tools will be employed: the Cochran - Mantel - Haenszel (CMH) test or nonparametric test, an independent samples t - test, and a two - sided test. Additionally, analysis of covariance, covariance analysis, generalized estimating equations, chi - square (
$x^{2}$
) tests, and linear regression will be applied to all available and appropriate data. A P - value <0.05 will be considered statistically significant.

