**Methods and analysis:**

This is a randomized, blinded interventional trial with four parallel groups. A total of 84 eligible participants will be randomly assigned to one of four groups: the paroxetine group, CHSGS group, CHSGS + paroxetine group, or placebo group. The primary outcomes are Intravaginal ejaculatory latency time (IELT) and Pre- and post-treatment brain fMRI scans. The Secondary Outcomes include Premature ejaculation profile (PEP), Chinese Index of Premature Ejaculation (CIPE) and TCM syndrome score.

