Therefore, in this protocol, we plan to perform a double-blind randomized controlled trial, aiming to:1. Compared with the placebo and paroxetine, CHSGS will be as the same effective to the treatment for APE.2. Compared with paroxetine alone, CHSGS and combination of drugs will be more effective due to its specific effects.3. Investigate the influence of paroxetine or/and CHSGS capsule treatment on the brain activities of patients with APE compared with that of placebo treatment by fMRI and analyze the possible correlations between the changes of cerebral activity and the improvement of clinical variables in each group so as to explore how the paroxetine and CHSGS capsule manages depression by modulating brain function to treat APE.

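### IELT is compared across several pairs of arms at an unadjusted P<0.05: tested pairwise and ungated, the chance of a false positive is about 13–20%, and the error over both primary outcomes is uncontrolled

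*Protocol article*

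**What the plan says.** **Primary outcomes.** The Abstract (Methods and analysis) says: "The primary outcomes are Intravaginal ejaculatory latency time (IELT) and Pre- and post-treatment brain fMRI scans". The Primary outcome section repeats that change from baseline "will be evaluated in two aspects: the brain MRI and the intravaginal ejaculatory latency time (IELT) measured using a stopwatch". Neither place says whether success needs one of these or both.

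**Arms and contrasts.** The Randomized section has patients "randomly allocated to one of four groups in a 1:1:1:1 ratio", so six pairs of arms are possible. Aim 1 in the Introduction reads: "Compared with the placebo and paroxetine, CHSGS will be as the same effective to the treatment for APE". Aim 2 expects CHSGS, and also the combination, to do better than paroxetine alone. Together, aims 1 and 2 name three distinct contrasts: CHSGS vs placebo, CHSGS vs paroxetine, and combination vs paroxetine.

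**Clinical analysis.** Clinical variables analysis lists a set of tools. It includes "an independent samples t - test, and a two - sided test" and "analysis of covariance, covariance analysis, generalized estimating equations, chi - square" tests, with linear regression and Cochran–Mantel–Haenszel or nonparametric tests. None is tied to IELT or to a contrast. The paragraph ends: "A P - value <0.05 will be considered statistically significant".

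**fMRI analysis.** Regional homogeneity analysis has a different rule. ReHo maps before and after treatment are compared by paired t-test within each group, at P<0.005 with clusters of more than 20 voxels. No family-wise or false-discovery-rate correction is stated.

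**Correlations.** Aim 3 also plans to "analyze the possible correlations between the changes of cerebral activity and the improvement of clinical variables in each group".

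**The concern.** The article fixes several confirmatory-looking IELT comparisons and one flat threshold, and nothing links the two. Because no contrast is decisive, a single nominal P<0.05 among several could be presented as evidence of efficacy. The aims widen this freedom: for CHSGS vs paroxetine, aim 1 expects equality and aim 2 expects superiority, so either result could be read as agreeing with the plan.

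The second primary outcome offers another route to a positive claim. It is a whole-brain search, run separately in four groups, with no stated correction over voxels or groups. What is at stake is whether a positive primary result from 84 patients carries the 5% error rate that readers will assume.

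**Working it through.** **Inputs from the document.** Four arms; 21 per arm included and 15 needed (Study design); threshold 0.05, two-sided (Clinical variables analysis); three contrasts from aims 1–2, six possible pairs. The document states no family-wise error rate or power, so there is no such figure to reproduce. Its one checkable total does reproduce: 4 × 21 = 84.

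**Step 1: reference values if the tests were independent.** Error = 1 − (1 − 0.05)^k.
- k = 3: 1 − 0.95³ = 14.3%
- k = 6: 1 − 0.95⁶ = 26.5%

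These overstate the error, because the contrasts share arms and so are correlated.

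**Step 2: allow for the shared arms.** Four arms were simulated with no true difference, normal outcomes and equal variances (200,000 runs), using two-sided independent t-tests at 0.05. The table shows the chance of at least one P<0.05 on IELT.

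| Contrasts tested | 21 per arm | 15 per arm |
|---|---|---|
| Three active arms vs placebo | 12.5% | 12.5% |
| Three in aims 1–2 | 12.9% | 13.0% |
| Those three plus paroxetine vs placebo | 15.5% | 15.5% |
| All six pairs | 20.2% | 20.2% |

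The result hardly depends on the arm size. It is about 2.5 to 4 times the nominal 5%.

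**Step 3: effect of simple remedies on IELT.**
- Three contrasts at 0.05/3 = 0.0167 each: simulated error 4.5–4.6%.
- Six contrasts at 0.05/6 = 0.0083 each: 4.1%.
- An omnibus F test at 0.05 before the pairwise tests: 4.2% (three aim contrasts) and 5.0% (six pairs) when all arms are equal. This gate does not hold in general. If only placebo differs from the other arms, the F test may pass and leave two null aim contrasts at 0.05 each, with error up to 1 − 0.95² = 9.75%.

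**Step 4: the fMRI primary.** Four single tests at 0.005 would give 1 − 0.995⁴ = 2.0%. A ReHo map is not a single test, however. The false-positive rate of a voxel-wise search with a 20-voxel extent depends on image smoothness and the number of voxels searched. The smoothing kernel is given, but the realised smoothness is not, so no figure follows from the document, either for fMRI or for both primaries together.

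**Step 5: per-group correlations.** No threshold is given for these. If 0.05 were used, significance would need |r| = t/√(t² + n − 2):
- n = 21: 2.093/√(2.093² + 19) = 0.433
- n = 15: 2.160/√(2.160² + 13) = 0.514

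For 80% power, the true r must be about tanh[(1.960 + 0.842)/√(n − 3)], which is 0.58 at n = 21 and 0.67 at n = 15. Only strong correlations could be detected within a group. With four groups and four clinical measures (IELT, PEP, CIPE, TCM score) there would be 4 × 4 = 16 tests per brain region.

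**The case against.** **Multiplicity rules often sit in the SAP or full protocol, and neither is shown.** This is fair, and the mere absence of a rule would be no finding. But the article does more than stay silent: it fixes a threshold and calls any result below it significant. Applied to its own aims, that rule inflates the error. A fuller plan may already repair this, and the point is limited accordingly.

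**The listed methods are not only two-sample tests.** This stands. ANCOVA, generalized estimating equations and regression can handle four arms, and an omnibus gate would bring the IELT error to 4–5% when all arms are equal. Nothing assigns such a model to IELT or makes it a gate, so the 13–20% is conditional on ungated pairwise testing.

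**A reader might combine the two primaries and infer 24–36%.** The arithmetic would be 1 − (1 − 0.129)² = 24.1% for three contrasts and 1 − (1 − 0.2023)² = 36.4% for six. The document does not support this. The 0.05 sentence belongs to the clinical variables; fMRI is tested within groups at P<0.005 with a cluster rule. The combined figure needs a between-arm scalar fMRI test at 0.05 that appears nowhere. It also assumes that the two outcomes are independent and that success on either suffices. If both had to succeed, the second outcome would add no inflation.

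**A reader might also take the brain–symptom correlations as fixed at P<0.05.** That would be an inference. Aim 3 is worded as exploration and names neither a test nor a threshold for them; Pearson correlation is mentioned only for the clinical scores. Their low power does not bear on the false-positive rate of the primary result.

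**Conclusion.** The point holds for IELT, conditionally. With the contrasts in the aims tested pairwise, ungated and at the stated 0.05, the chance of at least one false positive is about 13% for three contrasts, rising to 20% for all six pairs. These figures assume no true differences between arms, normal outcomes with equal variances, and equal arm sizes.

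For the two primaries together, the conclusion is qualitative: the error is uncontrolled, and the document gives no basis for a number. It is worth correcting before unblinding, and it does not call the design into question.

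**What to change.** 1. Analyse IELT in one four-arm ANCOVA adjusted for baseline. Then either test in a fixed order at two-sided 0.05 (CHSGS vs placebo, then combination vs paroxetine), or test the three aim contrasts at 0.0167 each (error about 4.5%). Report all other comparisons as estimates with confidence intervals.
2. State whether success needs either primary or both. If either suffices, alpha must also be shared between them. With an equal split, 0.025 goes to IELT, which means 0.025/3 = 0.0083 for each of three contrasts. If both must succeed, no sharing is needed.
3. Apply image-wise family-wise error control to the fMRI maps and say how the four groups are handled. fMRI need not lose its primary status for this.
4. Label the per-group brain–symptom correlations exploratory, with false-discovery-rate control over regions and scores.
5. Reconcile aims 1 and 2 on CHSGS vs paroxetine. A non-significant difference would not show equal effect.

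**Cost.** These are changes to analysis wording, with no new data. Under the fixed order, a later contrast cannot be claimed if an earlier one fails, and CHSGS vs paroxetine leaves the confirmatory set. Under 0.0167 all three contrasts stay, each with slightly less power. Image-wise correction will leave fewer regions significant.
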